#### **4.4 Withdrawal of Subjects**

A subject is free to withdraw from the study at any time for any reason without prejudice to their future medical care by the physician or at the institution. The investigator or Sponsor may also withdraw the subject at any time in the interest of subject safety. The primary reason for withdrawal must be recorded on the withdrawal form in the case report form (CRF). If a subject is withdrawn for more than 1 reason, each reason should be documented and the most medically significant reason should be noted on the CRF.

The withdrawal of a subject from the study should be discussed where possible with the Medical Monitor before the subject stops investigational product. If investigational product is discontinued, the final evaluations will be performed as completely as possible. Subjects who drop out of the study prior to obtaining endpoint data from hour 24 will be replaced by the next available subject. Any comments (spontaneous or elicited) or complaints made by the subject and the reason for termination, date of stopping investigational product, and the total amount of investigational product taken must be recorded in the CRF.

The Sponsor reserves the right to terminate the study at any time.

Reasons for withdrawal may include:

- If consent is withdrawn or the subject refuses to continue treatment and/or procedures/observations
- If the clinical condition under study requires alternative treatment
- Occurrence of unmanageable AEs or if the subject requires concomitant medication disallowed under this protocol (see Section 5.2)
- If the subject becomes pregnant
- For other reasons (eg, significant protocol violation or non-compliance)

At least 3 documented attempts must be made to contact any subject lost to follow-up, 1 of which must include sending a certified letter to the subject's last

known address, requesting that they return to the study site for final safety evaluations.

The Sponsor may be contacted if clarification is required on a case-by-case basis.

## **5 STUDY AND CONCOMITANT TREATMENTS**

### **5.1 GMI-1070**

The official product name, as indicated in the Investigator's Brochure, is 'GMI-1070 Injection, 30 mg/mL.' However, in order to allay any confusion regarding the route of administration in this protocol, the product has been referred to as 'GMI-1070.' For further details regarding the exact composition of the product, please refer to the Investigator's Brochure.

Investigational product will be supplied in vials, each containing 250 mg of liquid formulation of GMI-1070 at a 30 mg/mL concentration. Each study drug administration will occur over a period of 20 minutes from the start of the IV infusion, and will be followed by a saline flush.

The test product will be administered using 1 of the following dose regimens (2 doses total, administered at 0 and 10 ± 1 hours):

- Dose Level A, 20 mg/kg load followed by 10 mg/kg at 10 ± 1 hours
- Dose Level B, 40 mg/kg load followed by 20 mg/kg at 10 ± 1 hours
- Dose Level C, 10 mg/kg load followed by 5 mg/kg at 10 ± 1 hours
- Dose Level D, 5 mg/kg load followed by 2.5 mg/kg at 10 ± 1 hours

A written authorization (prescription/order/instruction) signed by an appropriately licensed physician, in this case the investigator, is required prior to providing any subject with investigational product.

Note: If enrollment at a site begins after other sites have enrolled in the study, the safety, PK, and blood flow information gained by early-enrolling site(s) may be used to modify dosing by later-enrolling site(s).

After Dose Level A has been administered to at least 4 subjects at one site, and this site's investigator and the Medical Monitor have determined it appropriate to proceed with another dose level as described above, a new site joining the study may proceed with either of the confirmed dose levels (Dose Level A, or the subsequent chosen dose level) if agreed by the new site's investigator and Medical Monitor.

### 5.1.1 Allocation of Subjects to Treatment

This is an open-label study in which subjects will be enrolled into dose levels on a first-come, first-served basis. The study will not be blinded or randomized.

### 5.1.2 Labeling, Packaging, Storage, and Handling

The investigational product will be shipped to a designee at the study site and must be stored in a pharmacy or locked and secured in a storage facility with temperature control, accessible only to those individuals authorized by the investigator or designee.

The Sponsor will supply sufficient quantities of IV GMI-1070 to allow completion of this study. The lot numbers, manufacture dates, and expiration dates (if available) of the drugs supplied will be recorded in the final report.

Investigational product will be supplied to the pharmacy in vials, each containing 250 mg of liquid formulation of GMI-1070 at a concentration of 30 mg/mL. Vials will be labeled with the following label:

[figure not shown]

Study drug must be refrigerated at a controlled temperature between 2° and 8°C. Temperature monitoring is required at the storage location to ensure that the investigational product is maintained within this temperature range. The investigator or designee is responsible for ensuring that the temperature is monitored throughout the total duration of the trial and that records are maintained; the temperature should be monitored continuously. Excursion from the established range will require site investigation as to cause and remediation. GMI will determine the ultimate impact of any excursions and will provide supportive documentation.

### 5.1.3 Compliance and Drug Accountability

Investigational product must be used only as directed in the protocol. The investigator or designee will be provided with forms to enable accurate, written records of all investigational product received from GMI. These records will be kept by the investigator, pharmacist, or designee of either individual.

At the end of the study, and only upon written authorization by GMI, all unused stock will be sent to a designated contractor on behalf of GMI. Investigational

products returned to GMI-designated contractors must be counted and verified by site personnel and GMI (or designated contract research organization [CRO]) prior to shipment. All certificates of delivery/drug receipts, and/or return forms must be signed prior to shipment. Investigational products for return must be packed in a tamper-evident manner to ensure integrity by receiving contractor. All investigational product returned must be in accordance with local, state, and national laws.

Based on entries in the site drug accountability forms, it must be possible to reconcile drug delivered with that used and returned. All investigational product must be accounted for and all discrepancies investigated and documented appropriately.

## **5.2 Concomitant Medications**

All concomitant medications should be recorded at Screening, confirmed predose, and recorded again during the study visits. Subjects currently taking anti-inflammatory agents or steroids will be excluded from enrollment. The use of hydroxyurea and NSAIDs will be allowed.

# **6 STUDY PROCEDURES**

## **6.1 Study Schedule**

Refer to the Schedule of Assessments, Table 1, for a complete list of procedures and times for each assessment.

### **6.1.1 Screening Visit**

The Screening Visit should occur within 30 days prior to initiation of treatment. All prospective subjects will have the study explained in non-technical terms by a member of the research team or a member of the clinic staff. The nature of the drug substance to be evaluated will be explained together with potential hazards involving possible adverse reactions. Written informed consent will be obtained from each subject prior to dosing.

Subjects will have to meet all inclusion/exclusion criteria before being enrolled in the study (see Section 4).

**6.1.2 Day of GMI-1070 Administration****6.1.2.1 Baseline**

Baseline evaluations will be performed the day of IV GMI-1070 dosing, prior to drug administration. Eligible subjects will be assigned to a specific dose level by the investigator, in accordance with the protocol (refer to Section 5.1.1).

**6.1.2.2 Dosing**

The weight measured at Screening will be used to determine the appropriate dose administered throughout the study. Subjects will be dosed with IV GMI-1070 for a total of 2 doses over  $10 \pm 1$  hours (as specified by dose level, refer to Section 5.1). GMI-1070 is supplied as sterile solution for infusion. Each study drug administration will occur over a period of 20 minutes from the start of the IV infusion, and will be followed by a saline flush.

The calendar date and 24-hour clock time of the beginning and end of each infusion will be recorded on the CRF.

**6.2 Study Evaluations and Procedures****6.2.1 Safety****6.2.1.1 Physical Examination**

A full physical examination includes a review of the following body systems:

- General Appearance
- Skin
- Head, Ears, Eyes, Nose, Throat
- Spine/Neck/Thyroid
- Respiratory
- Cardiovascular
- Abdomen (including liver and kidneys)
- Nervous System
- Musculoskeletal

A targeted physical examination includes body systems selected at the discretion of the investigator.

Any abnormalities or changes in intensity noted during the review of body systems should be documented and reported on the appropriate CRF page. If a new clinically significant finding (ie, not noted at screening) occurs at the baseline examination or subsequently, an AE form must be completed. In

addition, resolution of any abnormal findings during the study will be noted in the medical record and/or the CRF if clinically significant.

#### **6.2.1.2 Vital Signs**

Complete vital signs are considered to be body temperature, respirations, blood pressure, and pulse (taken after 5 minutes seated).

When the time of vital signs measurement coincides with a blood draw, the vital signs will be taken approximately 10 minutes before the scheduled blood draw.

#### **6.2.1.3 Electrocardiogram**

A 12-lead ECG will be performed according to standard procedure at the investigational site.

#### **6.2.1.4 Clinical Laboratory Evaluations**

All laboratory assays will be performed locally according to the laboratory's normal procedures. Reference ranges will be supplied by the local laboratory. Lab assays may be repeated once to rule out lab error, before determining if results are normal or abnormal. It is recognized that in SCD lab values that are out of the reference range may in fact be baseline for that individual. When test results are outside the reference range, the investigator will indicate on the CRF whether the result is considered to be clinically significant or not. Out of range results not considered to be clinically significant by the investigator will not be considered abnormal for the purposes of this study. Abnormal laboratory values which are unexpected or not explained by the subject's clinical condition should be repeated until confirmed, explained, or resolved. Data to be collected are noted below.

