#### **9.2.6 Vital Signs and Laboratory Parameters**

For vital signs and continuous laboratory parameters, the observed value and the change in the value from baseline at each collection point during the treatment phase will be presented. Values will be analyzed using a generalized linear mixed model over the longitudinal measurements. This model will allow comparisons of each secondary outcome over the treatment groups, controlling for time and baseline measurement as fixed effects and subject as a random effect.

For categorical laboratory parameters that are collected in terms of abnormal or normal or can be classified into positive or negative results, the number and percent of subjects having values in each category will be presented at each scheduled collection time. For those categorical laboratory parameters that are reported in several descriptive categories (eg, urinalysis color), the number and percent of subjects by each category will be presented. Graphs displaying population trends over time may be produced.

For both vital signs and laboratory parameters, clinically significant results will be listed with relevant subject information for assessment.

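### Section 6.2.1.4 lets the investigator's view of clinical significance decide whether an out-of-range laboratory result is abnormal, without reference to the subject's own baseline

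*Protocol*

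**What the plan says.** Section 6.2.1.4 has laboratory tests run locally against local reference ranges. It gives the background that "It is recognized that in SCD lab values that are out of the reference range may in fact be baseline for that individual". For a result outside the range, "the investigator will indicate on the CRF whether the result is considered to be clinically significant or not". It then fixes the definition: "Out of range results not considered to be clinically significant by the investigator will not be considered abnormal for the purposes of this study".

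Section 9.2.6 uses laboratory results in three ways:

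- For continuous parameters, "the observed value and the change in the value from baseline at each collection point during the treatment phase will be presented", followed by a longitudinal mixed model.
- For categorical parameters "collected in terms of abnormal or normal or can be classified into positive or negative results", the number and percent of subjects in each category are given at each collection time.
- For laboratory parameters and vital signs alike, "clinically significant results will be listed with relevant subject information for assessment".

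Section 7.1 says that when a change believed to come from SCD occurs after dosing starts, the investigator notes either that it is clinically significant, and so an adverse event, or that it is not. On allocation, section 5.1.1 states: "The study will not be blinded or randomized". Section 2.2.1 makes safety the primary objective.

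**The concern.** The rule merges two things that should be recorded apart: whether a value lies outside the reference range, which is a measurement, and whether it matters clinically, which is an opinion. The person giving the opinion knows the dose. The protocol states no criterion for clinical significance, and the synopsis plans three sites, so the threshold may differ between investigators.

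The stated reason concerns the subject's own baseline, but the rule never refers to it. A value that was in range before dosing and out of range afterwards can be declared not abnormal on judgement alone. Because the same judgement also governs the listing and part of the adverse event route, one decision can remove a new finding from several safety outputs at once.

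**Working it through.** There is no protocol figure to reproduce. Section 9.3.2 justifies the sample size in words, and no rate of out-of-range results is given. The check is a comparison of sections, followed by an illustration on assumed inputs.

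**1. Rule against reason.** Take a post-dose result that is out of range and judged not clinically significant.

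| Day 1 predose | Post-dose | Label under 6.2.1.4 | Covered by the SCD-baseline reason? |
|---|---|---|---|
| out of range | out of range, unchanged | not abnormal | yes |
| out of range | further out of range | not abnormal | no |
| in range | out of range | not abnormal | no |

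The label is the same in all three rows, but the reason supports only the first. The data to separate them exist: Table 1 schedules hematology, biochemistry and urinalysis at the Day 1 predose baseline and again on Days 2, 3 and 7, with a blood count also at 8 hours.

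**2. Outputs that depend on the judgement.**
- *Abnormal/normal counts (9.2.6).* These are planned only for categorical parameters. Most hematology and chemistry items in Table 2 are continuous, so this chiefly concerns urinalysis, and only where a parameter is recorded as abnormal or normal.
- *Listing (9.2.6).* The listing specified is of clinically significant results. A new out-of-range value judged otherwise is not in it.
- *Adverse events (7.1).* For changes believed SCD-related, the same judgement decides whether the change becomes an adverse event.

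**3. Outputs that do not depend on it.**
- Observed values and changes from baseline of continuous parameters (9.2.6). Section 9 requires the number of observations, mean, standard deviation and/or standard error, minimum and maximum, by dose level and time point.
- Dose decisions: Table 3 in section 6.2.5 has clinical laboratory data themselves reviewed after each group of 4.

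**4. Size, on assumptions only.** Let p be the true proportion of subjects with a new out-of-range result on a parameter counted as abnormal/normal, and q the share of those results called not clinically significant. Treat subjects as independent. The expected labelled count in 20 subjects is 20 × p × (1 − q). The chance that a group of 4 shows at least one is 1 − [1 − p(1 − q)]^4.

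| p | q | Expected of 20 | Chance of at least 1 in 4 |
|---|---|---|---|
| 0.20 | 0 | 4.0 | 0.59 |
| 0.20 | 0.25 | 3.0 | 0.48 |
| 0.20 | 0.50 | 2.0 | 0.34 |
| 0.20 | 0.90 | 0.4 | 0.08 |
| 0.40 | 0 | 8.0 | 0.87 |
| 0.40 | 0.25 | 6.0 | 0.76 |
| 0.40 | 0.50 | 4.0 | 0.59 |
| 0.40 | 0.90 | 0.8 | 0.15 |

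For example, with p = 0.20 and q = 0.50: 20 × 0.20 × 0.50 = 2.0, and 1 − 0.90^4 = 0.34. The labelled count can only equal or fall below the true count, and the expected loss is the share q. The rows with q = 0 are the count by reference range.

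**The case against.** The strongest reply is that the label has little to act on. Continuous parameters never pass through it. Section 9.2.6 also tabulates positive/negative results and multi-category results by their own categories, which need no abnormal label, and dose decisions use the laboratory data directly. The significance judgement is already a CRF entry, and the layout of tables and listings may be left to the statistical analysis plan. Naming clinically significant results for a listing does not say that other results are withheld.

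Most of this stands, and it limits the point. A reader might infer that an ALT or creatinine rise in one of 4 subjects would be diluted to a quarter of its size in the mean and counted as none of 4 abnormal. The protocol does not support that. No abnormal/normal count is planned for those parameters, and the maximum change required by section 9 would show the full rise. Nor do the documents show that new abnormalities *will* be undercounted. Many out-of-range values in SCD are chronic, and the values of q above are assumed. With no control arm, there is also no comparison of arms to bias; the risk is incomplete and inconsistent recording.

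What the reply does not remove is the definition itself, which this protocol states rather than leaving to the analysis plan. A minimum or maximum also does not show whether a subject crossed from in range to out of range. Because ranges are local, an extreme pooled over sites cannot be read against a single limit.

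**Conclusion.** The point holds in a limited form. The definition in 6.2.1.4 is wider than its reason: it can take the label *abnormal* from a new or worsened post-dose value, not only from a stable SCD baseline value. Such a value can then be missing from an abnormal/normal count, from the planned listing and, if believed SCD-related, from the adverse events. The unfiltered continuous summaries and the direct laboratory review mean that it is not wholly hidden. The size of any undercount is unknown. This rests on reading the sentence as written and on no other document defining clinical significance or adding a fuller listing. It is worth correcting because it bears on the primary objective and the correction uses data already collected.

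**What to change.** In 6.2.1.4, replace the definition with: each result is classified as low, normal or high (or positive/negative) by the local reference range, and the investigator's judgement of clinical significance is recorded as a separate CRF flag that does not alter the classification.

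In 9.2.6, add a table of shifts from Day 1 predose to each visit, by dose level, and list every new or worsened out-of-range value with its flag.

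The repeat-testing sentence in 6.2.1.4 also uses the word *abnormal*, so the sponsor should state which meaning applies there once the definition changes. The adverse event judgement in 7.1 stays with the investigator; the fuller listing makes it visible.

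Cost: wording in two sections, one extra table and a longer listing. No new samples or CRF items are needed, since values, local ranges and the significance judgement are already collected. More results will be classed as out of range, but chronic SCD abnormalities will appear as no shift, which answers the protocol's own reason for the rule.

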**Table 2: Clinical Laboratory Evaluations**

|                           |                                             |
|---------------------------|---------------------------------------------|
| Hematology         |                                             |
| Hemoglobin                | Platelet count                              |
| Hematocrit                | WBC count with differential                 |
| RBC count                 | High sensitivity C-reactive protein (hsCRP) |
| Reticulocyte count        |                                             |
| Serum Chemistry    |                                             |
| Blood urea nitrogen       | ALT (SGPT)                                  |
| Creatinine                | AST (SGOT)                                  |
| Electrolytes with glucose | Total and Direct bilirubin                  |
|                           | Lactate dehydrogenase (LDH)                 |

|                                                                                                                                           |                    |
|-------------------------------------------------------------------------------------------------------------------------------------------|--------------------|
| Urinalysis                                                                                                                         |                    |
| pH                                                                                                                                        | Bilirubin          |
| Specific gravity                                                                                                                          | Blood              |
| Protein                                                                                                                                   | Nitrite            |
| Glucose                                                                                                                                   | Urobilinogen       |
| Ketones                                                                                                                                   | Leukocyte esterase |
| If urinalysis is positive for blood or leukocyte esterase, a microscopic examination for RBC, WBC, bacteria, and casts will be performed. |                    |

#### 6.2.1.5 Pregnancy Test

Female subjects should be either post-menopausal (amenorrhea for at least 12 consecutive months), surgically sterile, or women of child-bearing potential with a negative urine or serum beta human chorionic gonadotropin pregnancy test prior to entering the study and who are using or agree to use at least 1 acceptable method of contraception. Acceptable contraceptives include intrauterine devices, hormonal contraceptives (oral, depot, patch, or injectable) and double barrier methods such as condoms or diaphragms with spermicidal gel or foam.

Women of child-bearing potential must be advised to use acceptable contraceptives throughout the study period and for 30 days after the last dose of investigational product. If hormonal contraceptives are used, they should be taken according to the package insert. Women of child-bearing potential who are not currently sexually active must agree to use acceptable contraception, as defined above, if they decide to become sexually active during the period of the study and for 30 days after the last dose of investigational product.

At the Day  $28 \pm 3$  follow up telephone call, women of child-bearing potential will be asked if they have had a positive pregnancy test since taking place in the study. The response will be documented in the CRF. Any pregnancies will be handled as described in Section 7.1.

